### Exclusion criteria

Postoperative complications include infection, neurovascular injury, or symptomatic deep vein thrombosis.History of ipsilateral hip replacement, osteoarthritis, or pain of ipsilateral hip.Severe comorbidities include lower limb fracture, malignant tumor, cardiovascular disease, or neurological disease.Other reasons for exclusion (mentally unable to participate, etc.).

After randomization, the criterion for dropping out will be the participants not attending the assessments (4 weeks, and follow-ups).

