### Sample size

Based on the work being done by the team when formulating the plan, we estimated that the difference in TUGT time between the two groups was 1.87 s. With a 2-sided α error of 0.05 and a β error of 0.20, the sample size is estimated at 22 patients in each group. Due to a dropout rate of about 10%, 50 patients are needed.

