### Randomization procedure and concealment of allocation

Patients who meet the inclusion criteria and are willing to participate will be randomized in a 1:1 allocation ratio after the baseline assessment. SPSS25.0 (IBM Corp., Armonk, NY, United States) statistical software was used to generate random serial numbers. These serial numbers were then printed on cards, sealed in paper envelopes, and the same serial number was written on the outside of each envelope. Patients opened the envelopes in the order of their recruitment. The participants will be randomly divided into two groups: the experimental group (hamstring training group) consisting of 25 cases, and the control group (routine rehabilitation group) consisting of 25 cases. The allocation numbers were concealed in opaque sealed envelopes prepared by a central study coordinator. These envelopes will only be accessible to the central study coordinator, who will open them after obtaining informed consent and baseline measures.

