#### Statistical analysis

SPSS24.0 statistical software was used for the statistical analysis of the data in this study. Data were presented as mean (SD) or median [Q1–Q3] for quantitative variables and frequency (%) for categorical variables. The design includes two groups and three time points. The Shapiro–Wilk test is used to check the normality of the measurement data; if the data do not follow a normal distribution, transformations will be applied. A two-way ANOVA is conducted to determine whether there is an interaction between group and time factors. If an interaction is detected, we will assess whether time or group has an independent effect. If no interaction is detected, we will determine if there are any main effects. Post-hoc comparisons between groups at the same time points are adjusted using Bonferroni correction to ensure the overall type I error rate for each ANOVA does not exceed 0.05. Minimal clinically significant differences (MCID) were applied to compare the present results. The analyzes were conducted intention-to-treat by an independent statistician blinded to group allocation. The significance level is set at α = 0.05.

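### The two-way ANOVA serves the stated intention-to-treat principle poorly when about 10% of patients may miss a visit; a mixed model on all observed visits would serve it better

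*Protocol article*

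**What the plan says.** Four places in the protocol article bear on this.

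- **Statistical analysis, principle:** "The analyzes were conducted intention-to-treat by an independent statistician blinded to group allocation".
- **Statistical analysis, method:** "A two-way ANOVA is conducted to determine whether there is an interaction between group and time factors". The same section gives two groups, three time points and SPSS. It does not say whether the ANOVA is repeated-measures or plain factorial.
- **Exclusion criteria:** "After randomization, the criterion for dropping out will be the participants not attending the assessments (4 weeks, and follow-ups". Dropping out is thus defined by an outcome visit that did not take place, not by stopping treatment.
- **Sample size:** "the sample size is estimated at 22 patients in each group", and then "Due to a dropout rate of about 10%, 50 patients are needed".

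The section on minimizing missing data deals with prevention (education and telephone contact).

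**The concern.** The article plans for missed assessments and, in one paragraph, commits to both an analysis principle and a model. An ANOVA cannot use an outcome that was not observed. What it does with the patient's other visits depends on how it is run, and both usual ways have a cost.

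- **Repeated-measures form (one row per patient):** a single missed visit removes the whole patient. Someone who attends at week 4 and misses only the follow-up loses a TUGT and HSS result that was actually obtained.
- **Plain factorial form (one row per visit):** only the missing rows go, but the model takes a patient's three values as unrelated. The standard errors for the group and interaction tests are then wrong even if nobody misses a visit.

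With 25 patients per arm, each discarded result counts. Patients and therapists are unblinded and only one arm has the added training, so unequal loss is possible, although nothing in the article shows that it will occur.

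**Working it through.** **Inputs.** From Sample size: a 1.87 s TUGT difference, two-sided α 0.05, β 0.20, 22 per arm, about 10% dropout, 50 in total. From the randomization section: 25 per arm. From Statistical analysis: three visits, two-way ANOVA, SPSS. The article gives no SD.

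**1. The plan's own figure.** 22 / (1 − 0.10) = 24.4, rounded up to 25 per arm, so 50 in total. This reproduces the stated number. In reverse, 25 × 0.90 = 22.5 per arm with complete assessments. The 22 itself cannot be checked without an SD. Solving backwards for n = 22 gives an SD of about 2.16 to 2.21 s (normal approximation) or 2.11 to 2.16 s (t-test).

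**2. Repeated-measures form.** Missing either post-baseline assessment is read as dropping out, so the 10% is taken as the overall rate.
- Patients deleted: 0.10 × 50 = 5, leaving 45.
- If all five miss only the follow-up, 50 × 3 − 5 = 145 values per outcome are observed and 45 × 3 = 135 are used. The 10 discarded are 5 baseline and 5 week-4 values.
- If all five miss both later visits, 50 × 3 − 10 = 140 are observed and 135 are used. Only 5 baseline values are discarded, and no week-4 result.

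So between 0 and 5 observed week-4 results per outcome are lost, depending on the pattern of missed visits.

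**3. What that is worth for the week-4 TUGT comparison.** Using t-test power at the back-solved SD (2.11 to 2.21 s, an assumption), 25 per arm gives about 83 to 87% and 22 per arm about 78 to 82%. Deletion therefore costs at most about 5 percentage points. It gives up a gain and does not push the trial below its plan, because 22 per arm is what the plan was sized for.

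**4. Plain factorial form.** Let σ² be the variance at one visit and ρ the correlation between any two visits of one patient (taken as equal, for simplicity), with n per arm.
- Group effect averaged over three visits: the true variance is 2σ²(1 + 2ρ) / (3n); the ANOVA assumes 2σ² / (3n). With ρ above 0 the test is too liberal.
- Group difference in change between two visits: the true variance is 4σ²(1 − ρ) / n; the ANOVA assumes 4σ² / n. The interaction test, which the plan puts first, is too conservative.

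**5. Bias, as an illustration only.** Suppose 3 of 25 hamstring-arm patients are lost and would have been 2.16 s slower than those seen. The observed arm mean is then too favourable by 3/25 × 2.16 = 0.26 s, and 0.26 / 1.87 = 14% of the target difference. The number lost, the shift and the SD are all assumed.

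**The case against.** The strongest reply is that this is a journal article. Rules for missing values may be in a full protocol or analysis plan that is not shown, and their absence here is no fault. That is right. If those documents specify imputation before a repeated-measures ANOVA, the deletion in step 2 does not arise. The point therefore rests on the model the article does name, not on what it omits.

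Several stronger readings are tempting, and the documents do not support them.

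- **That the sample size shows a completer analysis.** Raising 22 to 25 per arm for expected loss is ordinary practice and compatible with intention-to-treat.
- **That the dropout definition removes people from the analysis.** It says when a participant counts as having dropped out and nothing about the analysis set.
- **That patients would not be analysed as randomised.** A missing value moves nobody to the other arm. Analysis by assigned arm and treatment of unobserved values are separate questions.
- **That the analysis is bound to be complete-case.** This holds only for the repeated-measures form. The factorial form uses all observed visits.
- **That about 19% would be lost.** That figure needs 10% missing at each of two visits independently (1 − 0.9² = 0.19). Read together, the Exclusion criteria and Sample size sections give about 10% overall.
- **That the hamstring arm must lose more patients.** The rule about discomfort or pain ends training, not assessment, and a patient who stops training but attends is not a dropout under the article's definition.

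It is also fair that a mixed model has no value for a missed visit either. It relies on data being missing at random and would not necessarily remove the shift in step 5. This is why a sensitivity analysis belongs with it.

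**Conclusion.** The concern holds in a limited form. The article pairs an intention-to-treat label with a model that, in one form, discards about 5 of 50 patients at the stated rate, together with up to 5 observed week-4 results per outcome. In the other form it ignores within-patient correlation. The article does not say which form is meant, and neither suits the principle as well as a readily available alternative.

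The size is moderate. The cost in power is at most about 5 percentage points for the week-4 TUGT comparison, under a back-solved SD. The 0.26 s figure shows how a few losses could matter in arms of 25; it does not predict the bias in this trial. The conclusion assumes that the 10% is overall loss and that no imputation step is specified elsewhere.

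**What to change.** In Statistical analysis, replace the two-way ANOVA with a likelihood-based linear mixed model with terms for group, visit and group-by-visit and a within-patient correlation structure. State that it includes all randomised patients in their assigned arm and every observed visit. Take the between-group contrasts at each visit from this model, keeping the planned Bonferroni adjustment.

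State that the model assumes missing values are missing at random. Add one sensitivity analysis in which missing hamstring-arm values are imputed progressively worse, and report the shift at which the conclusion changes.

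The cost is a few sentences and one additional analysis. No visits, patients or measurements are added. The price is an explicit missing-at-random assumption, which the sensitivity analysis then probes.

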#### Publication

The research findings will be shared in scientific journals, making them accessible to the orthopedics and rehabilitation community. Additionally, these findings will be discussed and debated at scientific conferences to encourage meaningful discourse.

## Discussion

The hamstrings are muscles that span both joints and play a role in knee flexion and hip extension when exerting force. As antagonists, the hamstrings and quadriceps work together to maintain knee joint stability. During walking, the eccentric contraction of the hamstrings can slow down the swing of the calf, preventing knee joint instability (22). Therefore, in early postoperative treatment, it is important to not only focus on strengthening the quadriceps, but also improve the muscle balance of the knee joint and exercise the hamstrings. Balanced muscle strength is crucial for smooth completion of human body movements. However, the quadriceps are naturally stronger than the hamstrings in the knee joint. If solely focus on quadriceps strength training, it can lead to an imbalance in muscle strength of the knee joint (23). To address this, it is necessary to also strengthen the hamstring muscles which is often overlooked in clinical rehabilitation and further worsen the problem. Study have shown that the older adults exhibits reduced quadriceps activation and increased hamstring activity compared to healthy young individuals of the same age and gender (24). This highlights the need to pay more attention to the impact of hamstring strength on knee joint stability in older adults patients. Insufficient hamstring strength can negatively affect the stability of the knee joint. For instance, during the concentric contraction of the quadriceps or the stretching of the lower limbs, the hamstrings contract eccentrically. If the hamstrings lack adequate eccentric control ability, they are unable to effectively stabilize the knee joint (25).

Conventional rehabilitation training typically focuses on concentric contraction resistance in muscle strength training. Previous research has indicated that eccentric contraction resistance can effectively enhance the strength of target muscles, sometimes even increasing strength by 30–40% (26). Studies have also found that eccentric training has benefits in increasing the cross-sectional area of muscles, promoting muscle fiber synthesis, and improving muscle strength (24). Additionally, a study by LaStayo discovered that cardiopulmonary oxygen consumption during eccentric contraction resistance training was lower (27). This implies that while eccentric exercise reduces cardiopulmonary oxygen demand by 20%, muscle strength increases rapidly due to improved metabolic efficiency. Therefore, under the same metabolic workload, eccentric contraction training can enhance muscle strength to a greater extent (28). A systematic review analysis conducted by Roig further supports the effectiveness of muscle eccentric contraction resistance exercise in increasing strength compared to normal concentric contraction resistance exercise. Roig also suggests that due to its ability to enhance muscle strength with minimal energy expenditure, eccentric contraction training may be more suitable for older adults patients with low exercise tolerance (29). Considering that most individuals undergoing TKA surgery are middle-aged and older adults patients, eccentric contraction resistance training may be more appropriate. Unlike traditional hamstring muscle training methods that involve the use of elastic bands and manual resistance training, this study incorporates the use of isokinetic strength training equipment. Postoperative hamstring training has historically been relatively simple, but it poses challenges in terms of training intensity control and risk of injury for patients. In recent years, with advancements in medical equipment, isokinetic muscle strength training equipment has been increasingly utilized in rehabilitation training.

Numerous studies have examined post-TKA rehabilitation and hamstring muscle training. However, this program represents the first study to investigate the application of hamstring muscle isokinetic eccentric contraction training specifically for TKA patients. The participants are divided into two intervention groups: one receiving routine physical therapy and the other undergoing hamstring isokinetic eccentric contractions. The purpose of this study is to assess walking function, knee function, and pain severity in patients with TKA. TUGT test and HSS primarily assesses the individual’s mobility, balance, neuromuscular function, and flexibility, which can reflect the participants’ walking function and knee joint function. To provide an objective evaluation, three-dimensional gait analysis technology was utilized, which is considered the ‘gold standard’ for analyzing gait problems. The use of functional 3D gait analysis will help to know whether the hamstring isokinetic eccentric exercise will influence on walking function after TKA or not. This analysis system allows for a more precise assessment of the effects of hamstring muscle isokinetic eccentric contraction on TKA patients’ walking function. Peak torque refers to the maximum torque produced when the muscle is contracted with maximum force. In this study, the BIODEX isokinetic muscle strength test training system will be used to assess the Peak torque of hamstring muscle strength before and after the treatment. The aim is to determine whether isokinetic eccentric exercise could increase hamstring muscle strength. The Knee joint position perception test is to judge whether there is improvement through its position sense. One aims of this project is to know whether the hamstring isokinetic eccentric exercise will influence on walking function after TKA or not. Thus Three-dimensional gait analysis is a key component of this study and will provide important results. Additionally, VAS was used to compare any changes in pain levels after the isokinetic eccentric training of hamstring muscles.

This study has certain limitations, including just a single center and lack of long-term follow-up. While the characteristics of intervention measures may not allow for therapist blinding, evaluator and data analyst blinding will be implemented to reduce bias as much as possible. To enhance the credibility of the conclusions presented in this paper, future research should aim to multi-center research and extend the follow-up period. This will provide further clarification on the clinical effectiveness of hamstring muscle isokinetic eccentric contraction training.

## Ethics statement

The studies involving humans were approved by the Ethics Committee of the Second Rehabilitation Hospital of Shanghai. The studies were conducted in accordance with the local legislation and institutional requirements. The participants provided their written informed consent to participate in this study.
